### Sample size

2.9

This study has been powered to demonstrate non-inferiority of CT LSIM compared to SPECT lung scintigraphy, with 90% power, assuming a percentage success estimated from a previous study, assuming 95% sensitivity and 95% specificity; a 10% non-inferiority margin and 11% discordant pairs. This proportion must be bigger than the non-inferiority margin of 10%. With 90% power and 5% two-sided significance and estimated prevalence of 60%, 290 cases are required (116 without the disease and 174 with the disease). The pilot study we will aim to recruit 100 cases which will contribute to the definitive trial. The analysis of the results of the pilot study will allow a more precise estimate of full trial size.

We perform approximately 260 SPECT lung scintigraphy scans a year for suspected CTED/CTEPH and we expect to recruit 50% of these patients based on studies on CTED/CTEPH patients previously done at our institution. Hence would expect to complete the pilot study recruitment (n = 100) in 1 year and the full study in approximately 3 years depending on recruitment rate and sensitivity/specificity results from the pilot study. A flow chart of study design is shown in Fig. 3.

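### The sample-size inputs contradict each other: 11% discordant pairs cannot occur if both tests are 95% accurate, and the rule given for it does not belong in planning

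*Protocol article*

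**What the plan says.** Section 2.9 (Sample size) of the protocol article states the aim as "This study has been powered to demonstrate non-inferiority of CT LSIM compared to SPECT lung scintigraphy, with 90% power". The planning values are "assuming 95% sensitivity and 95% specificity; a 10% non-inferiority margin and 11% discordant pairs". The next sentence gives the only reason for the discordance figure: "This proportion must be bigger than the non-inferiority margin of 10"%. The error rates are set by "With 90% power and 5% two-sided significance", and the "estimated prevalence of 60"% converts a stratum size into a total. The result is "290 cases are required (116 without the disease and 174 with the disease").

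The section does not say whether the 95% applies to one test or to both. It says that a success percentage came from an earlier study, but gives no data on discordance. It adds that the 100-patient pilot counts towards the definitive trial and will be used to refine its size.

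**The concern.** In a paired accuracy study, discordance is not free once the accuracy of each test is fixed. Within a disease stratum, a pair is discordant only when exactly one of the two tests is wrong, so discordance cannot exceed the sum of the two error rates. Two tests at 95% allow at most 10%, and the plan uses 11%.

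The reason given for 11% is a second problem. It turns a condition that holds under the null hypothesis into a requirement on the planning value. Discordance is the main input that the pilot can update. If the sentence stands, a pilot estimate of 10% or less would appear inadmissible, although 95% accuracy for both tests requires such a value.

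**Working it through.** **Inputs (all from section 2.9).** Margin 0.10; discordance 0.11; two-sided 5%, so z = 1.960; 90% power, so z = 1.2816; prevalence 0.60. The true difference is not stated and is taken as zero.

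**1. Reproduce the plan's figure.** For a paired comparison with true difference zero, n = (z₁ + z₂)² × discordance / margin².

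- (1.960 + 1.2816)² = 10.507
- 10.507 × 0.11 / 0.01 = 115.6, rounded up to 116 without disease (the smaller stratum)
- 116 / 0.40 = 290 in total; 290 × 0.60 = 174 with disease

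All three printed numbers are recovered. The variants tried do not recover them: one-sided 5% gives 95 (238 in total), using the null variance for the significance term gives 110 (275 in total), and an unpaired formula gives 100 per group. The match with a zero difference means that the tests are assumed equally accurate, so the natural reading is 95% for both.

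**2. Is 11% possible at 95% and 95%?** With equal accuracy, the discordant cells are 0.055 each.

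- Both correct: 0.95 − 0.055 = 0.895
- Both wrong: 1 − 0.895 − 0.11 = −0.005

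A negative probability is not a valid scenario. The ceiling is 0.05 + 0.05 = 0.10. If errors are independent given disease status, discordance is 2 × 0.95 × 0.05 = 0.095.

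**3. Where the rule comes from.** At a true loss of 10 points, the two discordant cells differ by 0.10, so their sum is at least 0.10. That is a bound at the null boundary. At a zero difference the two cells are equal and their sum can be any value from 0 to 0.10.

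**4. Effect on size and power, same formula.** Power = Φ(0.10 / √(discordance / n) − 1.960).

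| Discordance | Without disease needed | Total needed | Specificity power, n = 116 | Sensitivity power, n = 174 |
|---|---|---|---|---|
| 11% (as stated) | 116 | 290 | 90.1% | 97.8% |
| 10% (ceiling) | 106 | 265 | 92.6% | 98.6% |
| 9.5% (independent errors) | 100 | 250 | 93.8% | 99.0% |
| 5% | 53 | 133 | 99.8% | over 99.9% |

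**5. The other reading: 95% is SPECT only and 11% is kept.** The CT-LSIM error rate must then be at least 11% − 5% = 6%, so its accuracy is at most 94%. At 94% the true difference is 0.01.

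- Variance term: 0.11 − 0.01² = 0.1099
- Specificity power at 116: Φ(0.09 / √(0.1099 / 116) − 1.960) = 83.2%
- Needed for 90%: 10.507 × 0.1099 / 0.09² = 142.6, so 143 without disease

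**The case against.** The best defence is that the discrepancy is small and errs on the safe side. The section never says that both tests are at exactly 95%. At 94.5% each, which could be printed as 95%, the ceiling is 11%. Under the plan's own formula, every discordance feasible at 95% for both tests gives more than 90% power in each stratum. The size is also declared provisional, pending the pilot. Most of this stands, and it limits the consequence. It does not make the printed inputs compatible. Even at 94.5% each, 11% is reached only if the two tests are never wrong together. Nor does it repair the rule, which is true as a null-boundary bound but is used as a planning constraint.

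A reader might go further and infer that an impossible input leaves the design without its stated 90% power. The documents do not support that. Figures below 90% arise only from additions that the section does not make:

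- **A different test.** A paired score test gives about 88% for specificity at 9.5% discordance and about 84% at 11%. The article names no paired non-inferiority test, a choice commonly left to an analysis plan. Score-test power also depends on discordance: it is about 92% at 8%.
- **Joint power.** Treating the strata as independent, the plan's formula gives 88.1% for both endpoints together at 11% (0.901 × 0.978) and 91.3% at 10%. Section 2.9 does not claim joint power. Sizing the smaller stratum at 90% and accepting more in the larger one is ordinary practice.
- **Unequal accuracy.** The 83% in step 5 of the working requires CT-LSIM to be the less accurate test, which does not fit the zero difference behind 290.

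**Conclusion.** The inputs in section 2.9 are mutually inconsistent. The 290 follows arithmetically from 11% discordance and a zero difference, but 11% is one point above the maximum that 95% accuracy for both tests allows. The justification is misapplied and would wrongly restrict the re-estimation from the pilot.

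On the natural reading, the trial is modestly oversized under its own formula, by at least 290 − 265 = 25 patients, and is not underpowered. Only the alternative reading, with SPECT at 95% and CT-LSIM at 94% or lower, takes specificity below 90%. The article should therefore say which reading it means.

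These conclusions rest on the normal-approximation paired formula that reproduces the plan's numbers, one-sided 2.5% testing, and a realised prevalence of 60%. The documents contain no discordance data, so 10% is a ceiling and 9.5% an illustration under independent errors. Neither is an estimate.

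**What to change.** - State the accuracy assumed for CT-LSIM and for SPECT separately, for sensitivity and for specificity.
- Replace 11% by a discordance compatible with those values (at most 10% if both tests are at 95%), and say how it was chosen.
- Delete the sentence requiring discordance to exceed the margin as a planning constraint. If it is kept for information, say that it describes the null boundary only.
- Keep 290 and report power separately for specificity (n = 116) and sensitivity (n = 174) under the paired test that will be used. With the present formula, these are about 93–94% and about 99% at 9.5–10% discordance.
- Re-estimate the size from the pilot's observed discordance, without a 10% floor.

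The cost is a few rewritten sentences and restated figures. Recruitment, margin and significance level do not change.

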**Fig. 3 fig3:**
[figure not shown]
Flow chart diagram of study design. CTED; chronic thromboembolic pulmonary disease, CTEPH; chronic thromboembolic pulmonary hypertension.

### Statistical analysis

2.10

A Statistical Package for the Social Sciences Program (SPSS) version 24 for Windows (SPSS Inc. Chicago, IL) will be used for statistical analysis. Continuous variables will be expressed as mean ± standard deviation (SD) for parametric variables and median (interquartile range) for non-parametric variables. Categorical data will be presented as the number of subjects and percentage.

A Chi-squared test will be used to establish sensitivity, specificity, positive and negative predictive values for detecting the presence and absence of PE. The Kappa (*κ*) statistic will be used to determine the level of agreement between the independent observers. The *κ* value will be defined as follows: values < 0 indicated lack of agreement; 0–0.20, slight agreement; 0.21–0.40, fair agreement; 0.41–0.60, moderate agreement; 0.61–0.80, substantial agreement; 0.81–1, almost perfect agreement.

All statistical tests will be two sided with a p value of less than 0.05 considered to be statistically significant.

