## Abstract

Chronic thromboembolic pulmonary hypertension (CTEPH) is a severe but treatable disease that is commonly underdiagnosed. Computed tomography lung subtraction iodine mapping (CT-LSIM) in addition to standard CT pulmonary angiography (CTPA) may improve the evaluation of suspected chronic pulmonary embolism and improve the diagnostic pick up rate. We aim to recruit 100 patients suspected of having CTEPH and perform CT-LSIM scans in addition to the current gold standard test of nuclear medicine test (lung single photon emission computed tomography (SPECT) imaging) as a pilot study which will contribute to and inform the definitive trial. The diagnostic accuracy of CT-LSIM and lung SPECT will be compared. The primary outcome of the full definitive study is non-inferiority of CT-LSIM versus lung SPECT imaging.

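### The only accuracy analysis named in Section 2.10, a chi-squared test at two-sided p<0.05, neither estimates sensitivity and specificity nor tests the paired 10-point non-inferiority hypothesis behind the 290 patients

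*Protocol article*

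**What the plan says.** - **Objective.** The Abstract states: "The primary outcome of the full definitive study is non-inferiority of CT-LSIM versus lung SPECT imaging". Section 2.9 (Sample size) agrees: "This study has been powered to demonstrate non-inferiority of CT LSIM compared to SPECT lung scintigraphy, with 90% power".
- **Planning inputs.** Section 2.9 works from "assuming 95% sensitivity and 95% specificity; a 10% non-inferiority margin and 11% discordant pairs", and concludes: "With 90% power and 5% two-sided significance and estimated prevalence of 60%, 290 cases are required". It splits these into 116 without and 174 with the disease. The pilot of 100 is to count towards the definitive study.
- **Pairing.** Each patient has CT-LSIM as well as SPECT, and the Discussion describes a head-to-head comparison.
- **Analysis.** Section 2.10 (Statistical analysis) gives one method for accuracy: "A Chi-squared test will be used to establish sensitivity, specificity, positive and negative predictive values for detecting the presence and absence of PE". The decision rule is: "All statistical tests will be two sided with a p value of less than 0.05 considered to be statistically significant". Kappa is named for reader agreement only. The section mentions no margin, no paired method and no confidence interval.
- **Hypothesis.** Section 1.1.1 (Aims and objectives) words the primary hypothesis as superiority in sensitivity over both V/Q SPECT and CTPA.
- **Reference standard.** The Abstract, Introduction and Discussion call SPECT the gold or reference standard. The article names no other.

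**The concern.** The sample size rests on one kind of analysis and the analysis section names another. Sensitivity, specificity and predictive values are proportions, to be estimated with intervals; a chi-squared p-value does not supply them. Non-inferiority needs a null hypothesis placed at the margin and, because the same patients have both tests, a variance built from the discordant pairs. Two-sided p<0.05 from a chi-squared test has neither. A significant result would not show that any loss is under 10 points, and a non-significant result would not show it either. Followed as written, Section 2.10 cannot deliver the conclusion that the Abstract promises.

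**Working it through.** **1. Which analysis does 290 belong to?** Inputs from Section 2.9: margin 0.10, discordant proportion 0.11, power 90%, two-sided 5%, prevalence 60%.

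Paired formula: n = (z₀.₉₇₅ + z₀.₉₀)² × discordance / margin² = 10.507 × 0.11 / 0.01 = 115.6, rounded up to 116.

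Taking 116 as the non-diseased group: 116 / 0.40 = 290 in total, and 290 × 0.60 = 174 diseased. All three stated figures are reproduced. The alternatives tried do not match: one-sided 5% gives 95, and the unpaired formula at 95% v 95% gives 100 per group. So 290 presupposes a paired analysis against an absolute margin of 10 points.

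**2. Reading A: chi-squared of each test against disease status.** Take a poor test with 60% sensitivity and 60% specificity, in 174 diseased and 116 non-diseased patients.
- Positive rates are 0.60 and 0.40, a difference of 0.20.
- Pooled rate = (174 × 0.60 + 116 × 0.40) / 290 = 0.52.
- Null SE = √[0.52 × 0.48 × (1/174 + 1/116)] = 0.0599. Alternative SE = √[0.24/174 + 0.24/116] = 0.0587.
- Power = Φ[(0.20 − 1.96 × 0.0599) / 0.0587] = Φ(1.41), about 92%. Simulation agrees.

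Significance therefore says almost nothing about how good the test is, and on this reading no test of CT-LSIM against SPECT is stated.

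**3. Reading B: chi-squared of CT-LSIM against SPECT.** Suppose CT-LSIM is truly at the margin: SPECT 95%, CT-LSIM 85%, with 11% discordance. The cells are SPECT right only 0.105, CT-LSIM right only 0.005, both wrong 0.045, both right 0.845. The pilot group sizes follow from 60% prevalence: 100 × 0.40 = 40 and 100 × 0.60 = 60. Share of 200,000 simulated studies with a non-significant result:

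| n in group | Unpaired chi-squared | McNemar |
|---|---|---|
| 40 (pilot, non-diseased) | 72% | 47% |
| 60 (pilot, diseased) | 57% | 24% |
| 116 (full, non-diseased) | 18% | 3% |
| 174 (full, diseased) | 4% | 0.2% |

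A 95% interval compared with the margin has a nominal false-acceptance rate of 2.5%. The gap between the columns is the effect of ignoring the pairing. McNemar's test repairs the pairing but still has its null at zero, so it cannot replace a margin-based analysis.

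**4. Does a margin-based paired analysis need more patients?** Power = Φ(0.10 / √(0.11/n) − 1.96).
- n = 116: Φ(3.247 − 1.960) = 90.1% for specificity.
- n = 174: Φ(3.977 − 1.960) = 97.8% for sensitivity.
- Both together, in separate patients: 0.901 × 0.978 = 88%.
- Pilot alone: about 48% (n = 40) and 65% (n = 60).

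The planned 290 is already the number for this analysis. In the step 3 scenario, a simple Wald interval for the paired difference accepted about 5% at both 116 and 174, twice the nominal rate. That is a reason to prefer a score interval.

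**The case against.** **The article does not say that chi-squared will compare the two tests.** This stands. The more natural reading is a table of each test against disease status, where pairing does not arise. A reader might infer that an unpaired comparison of CT-LSIM with SPECT is planned; the text does not support that. What remains on the natural reading is that the wrong tool is named for estimating accuracy and that nothing in Section 2.10 connects to the hypothesis in Section 2.9.

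**The article does not say that p≥0.05 will count as non-inferiority.** This also stands. The acceptance rates in step 3 are conditional on that misreading and do not describe a declared rule. They also depend on discordance. With independent errors (0.95 × 0.15 + 0.05 × 0.85 = 18.5% discordant) they would be 65%, 54%, 25% and 10%, but Section 2.9 states 11%.

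**The detail may be left to an analysis plan that is not shown.** That would excuse silence. It does not excuse a method that is stated and does not fit the stated hypothesis.

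**A two-sided p<0.05 suits the superiority hypothesis in Section 1.1.1.** Partly true, but that comparison is paired as well, and the hypothesis conflicts with the non-inferiority aim in the Abstract and Section 2.9.

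**The present stage is a pilot.** True, and the Abstract assigns non-inferiority to the definitive study. But the pilot patients count towards that study and inform its size, so the rule should be settled before their results are seen.

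**Conclusion.** The point holds. On either reading, the one accuracy method in Section 2.10 cannot yield the non-inferiority conclusion for which the study is sized, and it does not estimate the quantities it is said to establish. That conclusion rests on the text alone. The sizes rest on assumptions. The 92% assumes a 60%/60% test at the full planned numbers. The 72%, 57%, 18% and 4% assume a true 10-point deficit from 95%, 11% discordance, an unpaired comparison, and non-significance read as non-inferiority; the article states neither of the last two. The sample size is not at fault on this point, since 290 already corresponds to a paired, margin-based analysis. The correction should be made before pilot results are analysed, because the primary conclusion depends on it.

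**What to change.** Replace the chi-squared sentence in Section 2.10 with the following content:
- Report sensitivity, specificity, PPV and NPV for each test with 95% confidence intervals.
- Primary analysis: the paired difference, CT-LSIM minus SPECT, in sensitivity among diseased patients and in specificity among non-diseased patients. Give each a two-sided 95% confidence interval for paired proportions, for example a paired score interval. Conclude non-inferiority only if both lower limits exceed -10 points.
- Use McNemar's test for any superiority comparison.

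Two things must be settled for this to work:
- **Reference standard.** Disease status must come from a standard separate from both tests. If SPECT defines disease, its sensitivity and specificity are 100% by construction and the paired comparison has no meaning.
- **Primary hypothesis.** The superiority wording in Section 1.1.1 must be reconciled with the non-inferiority aim in the Abstract and Section 2.9.

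Cost: a wording change and a short script, since a paired score interval may lie outside the basic SPSS menus. N stays at 290.

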## Discussion

3

The INSPIRE study is a single centre prospective observational study which will aim to assess the sensitivity and specificity of CT-LSIM compared to CTPA and SPECT imaging in the diagnosis of CTEPH. It will also assess the performance of CT-LSIM in the evaluation of lung perfusion compared to the previous imaging modalities in CTEPH patients.

INSPIRE is the first study to compare the specificity and sensitivity of CT-LSIM to CTPA and SPECT imaging in the diagnosis of CTEPH. The only other study which assessed the diagnostic performance of CT-LSIM was conducted by Tamura et al. [7] comparing the diagnostic performance of CT-LSIM to CTPA using SPECT as a reference standard in 50 patients with CTEPH. The authors concluded that CT-LSIM is a feasible technique for the assessment of segmental lung perfusion in patients with CTEPH and provides a higher diagnostic accuracy compared to CTPA. Of note, Tamura et al. [7] only compared CT-LSIM to CTPA. Furthermore, SPECT imaging was based on lung perfusion only with no assessment of ventilation. The sample size is also small to draw any generalizable conclusions which was acknowledged as a limitation of the study. INSPIRE is the first study to provide a head to head comparison of CT-LSIM with SPECT which is the current gold standard in a large cohort of patients. The aim of the INSPIRE study is to become a multicentre study following the initial single centre pilot phase and recruit approximately 300 patients who are diagnosed or suspected to have CTEPH.

Previous studies have compared dual energy CT (DECT) [[8], [9], [10]], CTPA [11] and 3-D contrast enhanced lung perfusion MRI [12] to SPECT imaging for the evaluation of segmental lung perfusion in patients with CTEPH. These studies showed superior diagnostic performance of DECT compared with SPECT but not CTPA. However, despite DECT proving to be superior to SPECT imaging, the latter remains the reference standard perhaps due to the small number of patients included in these studies and because of lack of access to DECT due to the high cost.

CTPA, although offers an improved better spatial resolution and additional morphological information compared to nuclear medicine scintigraphy, it has lower sensitivity in detecting peripherally located perfusion defects compared to SPECT. Thus, SPECT imaging remains superior to CTPA despite the latter showing higher specificity [13].

CTEPH is a life shortening complication of acute PE which results in the formation of intravascular scars leading to increased pulmonary hypertension [14]. Currently, the gold standard treatment for these lesions is PEA in patients deemed fit for surgery and for proximal disease [15]. For patients who are unfit for surgery and for lesions which are inaccessible surgically such as segmental and subsegmental disease, balloon pulmonary angioplasty (BPA) has been recently introduced as a treatment option [16,17]. Therefore, pre BPA planning of segmental perfusion is essential and currently is assessed by a combination of CTPA and SPECT. INSPIRE hypothesise that CT-LSIM has the potential to offer a more accurate visualisation and assessment of lung segmental perfusion as pre-treatment planning tool for patients eligible for BPA.

The results of this study are important as CT-LSIM has the potential to cut down the cost of having two investigations (CTPA and SPECT), reduce the radiation dose by approximately 3–4 mSV and can be a one stop investigation reducing the number of patients visits to hospital from two to one visit.

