## Introduction

1

Chronic thromboembolic pulmonary hypertension (CTEPH) is a treatable, life-threatening disease that occurs in up to 4% of patients following acute pulmonary embolism (PE) [1]. The disease is characterised by remodelling of the pulmonary arteries due to poor clearance of clot. Prognosis is very poor without treatment, and pulmonary endarterectomy (PEA) is well established as the definitive and potentially curative treatment method for CTEPH.

The European Society of Cardiology recommends ventilation/perfusion single photon emission tomography (V/Q SPECT) as the first line-screening test for patients with CTEPH. The perfusion image involves injection of 99mTc labelled macroaggregated human albumin, exposing the patient to ionizing radiation and the study acquisition time is 30–40 min.

Evaluation of the pulmonary arterial tree by computed tomography pulmonary angiography (CTPA) and lung perfusion is required to determine the appropriate treatment strategy in chronic thromboembolic disease (CTED). Recently, there has been much interest in the application of lung perfused blood volume images using dual-energy CT (DECT) to assess lung perfusion [2,3]. However, DECT is not widely available in hospitals across the UK and V/Q SPECT remains the reference standard. The rationale, methodology and design of the IodiNe Subtraction mapping in the diagnosis of Pulmonary chronIc thRomboEmbolic disease (INSPIRE) study are summarised in this paper.

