#### Aims and objectives of the INSPIRE study

1.1.1

The main objective of the INSPIRE study is to assess the diagnostic performance of CT-LSIM for evaluation of pulmonary perfusion in patients with known or suspected CTEPH. The primary hypothesis is that CT-LSIM is more sensitive than V/Q SPECT and CTPA in the assessment of CTED in patients with known or suspected CTEPH. We also hypothesize that the diagnostic performance of the experienced observers will be better than the less experienced and that the number of alternate diagnoses made on CT-LSIM will be higher and more accurate than lung SPECT imaging.

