### Design and setting

2.1

The INSPIRE study is a single centre cross sectional observational diagnostic study comparing the diagnostic accuracy for new test CT-LSIM with nuclear medicine SPECT. The setting of the study is a tertiary referral centre for pulmonary hypertension. Patients will be recruited during their admission to the Sheffield Pulmonary Vascular Disease unit. CT scans will be performed in the Radiology Department at the Royal Hallamshire Hospital. Patients will be identified by the Pulmonary Hypertension team from their clinic visit as suspected CTED or CTEPH. Patients will be sent information sheets and written informed consent and those will be obtained from all the patients. Consent will be taken by a research team member on admission for diagnostic visit that includes CT scanning. The study is registered on clinicaltrials.gov (NCT03806907).

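### SPECT is both the comparator and the only named reference standard, while the primary hypothesis and the sample size need a third standard that the article does not name

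*Protocol article*

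**What the plan says.** All references are to the protocol article.

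**SPECT as comparator.** The Abstract states: "The primary outcome of the full definitive study is non-inferiority of CT-LSIM versus lung SPECT imaging". Section 2.1 describes a study "comparing the diagnostic accuracy for new test CT-LSIM with nuclear medicine SPECT", and section 2.9 powers non-inferiority against SPECT.

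**SPECT as standard.** The Abstract calls it the "current gold standard test of nuclear medicine test (lung single photon emission computed tomography (SPECT) imaging"). The Introduction says that "V/Q SPECT remains the reference standard". The Discussion puts both roles in one sentence: "INSPIRE is the first study to provide a head to head comparison of CT-LSIM with SPECT which is the current gold standard".

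**Primary hypothesis.** Section 1.1.1: "CT-LSIM is more sensitive than V/Q SPECT and CTPA".

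**Sample size.** Section 2.9 assumes 95% sensitivity and 95% specificity, a 10% margin, 11% discordant pairs, 90% power, 5% two-sided significance and 60% prevalence. It concludes that "290 cases are required (116 without the disease and 174 with the disease").

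**Analysis.** Section 2.10 plans sensitivity, specificity and predictive values but does not say what establishes that disease is present. The consensus read in section 2.8 covers CT-LSIM and CTPA only and is not presented as a final-diagnosis panel.

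**The concern.** Sensitivity and specificity need a definition of who has the disease. To compare two tests on these measures, that definition must allow either test to be wrong. Here the only standard named is one of the two tests being compared.

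If SPECT supplies the definition, three things follow. SPECT cannot be wrong, so CT-LSIM can at best equal its sensitivity and the hypothesis in section 1.1.1 cannot be confirmed at any sample size. A true defect seen only on CT-LSIM counts as a false positive, which penalises the new test for the advantage claimed for it. And the power calculation in section 2.9 no longer describes the comparison being made.

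The pilot is affected too. Its 100 cases are to count towards the definitive study and to refine its size, so the definition of disease used in the pilot carries forward.

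**Working it through.** **1. Reproducing the plan's figure.** Inputs from section 2.9: discordance 0.11, margin 0.10, 5% two-sided significance, 90% power, prevalence 0.60.

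Paired non-inferiority with a true difference of zero: n = (1.960 + 1.282)² × discordance / margin² = 10.507 × 0.11 / 0.01 = 115.6, so 116.

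- Total: 116 / 0.40 = 290.
- With disease: 290 × 0.60 = 174.

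All three stated figures reproduce, so the arithmetic is not at fault.

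**2. What that formula presupposes.** Zero net difference with 11% discordance means that, among the diseased, pairs positive only on CT-LSIM are as frequent as pairs positive only on SPECT. If SPECT defines disease, the first kind cannot occur among the diseased. The model therefore implies a standard other than SPECT.

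**3. Power if SPECT is the standard.** The comparison becomes one-sample: does the lower 95% limit for the agreement of CT-LSIM with SPECT exceed 90%? Take true agreement of 95% and the plan's group sizes, and sum exact binomial probabilities over the passing results.

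| Group | Interval | Most disagreements that still pass | Power |
|---|---|---|---|
| n=174 | Wilson or exact | 9 | 63% |
| n=174 | Wald | 11 | 84% |
| n=116 | Wilson or exact | 5 | 47% |
| n=116 | Wald | 6 | 64% |

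None of these reaches 90%.

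**4. How an equally good test would look against SPECT.** Assume both tests are truly 95%/95% and prevalence is 60%. SPECT-positive share: 0.6×0.95 + 0.4×0.05 = 0.59. SPECT-negative share: 0.41.

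*Independent errors* (discordance 2×0.95×0.05 = 9.5% in each group):

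- Apparent sensitivity = (0.6×0.95² + 0.4×0.05²)/0.59 = 0.5425/0.59 = 91.9%.
- Apparent specificity = (0.4×0.95² + 0.6×0.05²)/0.41 = 0.3625/0.41 = 88.4%.

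The specificity lies outside the 10-point margin.

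*Correlated errors, 5% discordance* (both right 92.5%, both wrong 2.5%):

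- Apparent sensitivity = (0.6×0.925 + 0.4×0.025)/0.59 = 0.565/0.59 = 95.8%.
- Apparent specificity = (0.4×0.925 + 0.6×0.025)/0.41 = 0.385/0.41 = 93.9%.

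Both lie inside the margin. The plan's 11% is nearer the independent case. It cannot be matched exactly, because two tests that are each 95% correct can disagree in at most 5% + 5% = 10% of patients.

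**The case against.** The strongest objection is that the article never says the accuracy tables will be scored against SPECT. Gold standard and reference standard may simply mean current practice. The Discussion says that dual-energy CT proved superior to SPECT while SPECT remains the reference standard, which would make no sense if the term meant the truth used for scoring. The Abstract speaks of comparing the accuracy of both tests, and section 2.9 counts patients with and without disease. The Discussion also sets INSPIRE apart from an earlier 50-patient study that did use SPECT as its reference. A third standard may well be intended and stated in the full protocol or in Fig. 3, neither of which is shown.

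Much of this stands. A reader might infer that the sensitivity comparison is decided by construction and that CT-LSIM can never be shown more sensitive. The document does not support that as a statement of fact; it follows only if SPECT is used to define disease. The power figures carry the same condition. The statement that an equally good test would miss the margin also depends on how far the errors of the two tests are correlated.

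The objection does not remove the conflict in the text. The only standard named is the comparator, and the hypothesis and sample size cannot be carried out against it. That is a contradiction between statements the article makes, and more than a detail left to another document.

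**Conclusion.** The primary comparison is internally inconsistent: SPECT is the comparator and the only named standard, while the hypothesis and the paired sample size need a standard against which SPECT can err. This part rests on the text alone.

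The size of the consequence is conditional. If SPECT defines disease, greater sensitivity of CT-LSIM cannot be shown. Power at 95% agreement is then about 63% to 84% in the group of 174 and 47% to 64% in the group of 116, the range reflecting the interval method. The apparent accuracy of an equally good CT-LSIM would run from 91.9%/88.4% with independent errors to 95.8%/93.9% at 5% discordance. These last figures also assume that the 95%/95% in section 2.9 applies to both tests, which the article does not say. If an independent standard is in fact used, these losses do not arise and the article needs to name it.

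**What to change.** In sections 2.8 to 2.10, adopt one of two courses.

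**(a) Name an independent standard.** Define disease by a final diagnosis that does not use the SPECT or CT-LSIM result, where the existing record allows it, and score both tests against it. Section 2.2 admits patients who clinically require SPECT and CTPA, and section 2.4 derives CT-LSIM from the CTPA. The recorded diagnosis has therefore probably been informed by these tests, and the residual incorporation bias should be acknowledged. Cost: the diagnosis has to be abstracted and perhaps re-adjudicated, and some diagnoses will remain uncertain or partly dependent on the tests.

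**(b) Restate the aim as agreement.** Make the primary aim positive and negative percent agreement of CT-LSIM with SPECT, remove from section 1.1.1 the claim of greater sensitivity than V/Q SPECT, and restate the power for the one-sample comparison with the interval method named. Cost: wording only, but the claim is weaker and the power at 290 patients falls below the stated 90% at 95% agreement.

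Under either course, the Abstract, Introduction and Discussion should say whether gold or reference standard means current practice or the definition of disease. The choice should be fixed before the pilot data are analysed.
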